### Intervention

#### Overall

The aim of the intervention is to achieve higher levels of physical activity and subsequent improvements in clinical variables including HbA1c, fatty acids, anthropometric variables, and lifestyle factors, through use of a digital platform (for the care giver) and smartphone-app (for the patients) during 12 weeks. The app is compatible with both Android (version 4.1 or higher) and iOS (version 9.2 and higher).

#### Download

The intervention group will download the DiaCert smartphone-app which is connected to a digital platform where the care giver can follow the activity (daily steps) of each individual user. The app is demonstrated and downloaded at the introductory baseline meeting. An individual user account for each study participant is created by the study personnel on the digital platform where data is stored. Unique and temporary 6-digit codes are used to ensure a secure connection to the app for each participant. The individual access codes are created by study personnel and communicated to participants via telephone 7 days after the introductory meeting to avoid overlap with baseline accelerometer measurements. Daily steps measured by the smartphone are thereafter registered and displayed automatically in the app.

After 12 weeks of usage, participants in the intervention group are asked to remove the app from their phones and respond to a short questionnaire including 16 questions about using the app. At the 6-month follow-up, all participants (both in the intervention and control group) are offered to download and connect to the app.

### The DiaCert smartphone-app

#### Individual step-goal

When study participants are connected to the DiaCert-app, an individual step-goal between 1000 and 10,000 steps is set together with study personnel. The step goal is set in discussion with each participant based on their usual activity level. The goal is thereafter revised every two weeks. Participants are contacted by study personnel and given the opportunity to increase their step goal by an even 500 steps if they wish, e.g. participants may increase their goal by, 500, 1000, 1500, 2000, etc. steps at revision. They may also keep the same goal. The maximum goal set at baseline or during follow-up is 10,000 steps.

#### Feedback and presentation of steps

Each day where the goal is achieved, the user will receive a positive feedback message saying “Well done, you have reached your step-goal”. Days when the goal is fulfilled are also marked in the app. On the first page of the app, steps from the last 7 days are visually displayed in circles that “fill-up” during the day as the user works towards the total daily step goal. When the goal is reached the circle has changed from empty (white) to filled (completely blue) and is marked with a check mark. The average number of total daily steps during the last 7 days is also shown here. Further, users can follow their daily steps from all days during which the app has been used in a bar chart. A day when the step goal is fulfilled is displayed as green bar in the chart while days when the goal is not fulfilled are displayed as red bars in the same chart.

#### Display of HbA1c levels

In the DiaCert-app, patients can also follow their HbA1c levels. Data is entered manually into the app for each participant by study personnel. Information on HbA1c analyzed within the intervention are displayed (date and HbA1c mmol/mol) in a chart in the DiaCert-app.

### Sample size and power considerations

Power calculations were performed prior to study start to ensure sufficient power to detect a clinically significant difference in the primary outcome (accelerometer measured physical activity). A total of 200 patients (100 in each group) completing the study would provide sufficient statistical power (80%) at the two-sided 5% significance level to detect a difference in moderate-to-vigorous activity of 8 min/day (e.g. 22 min/day vs. 30 min/day). A standard deviation of ±20 min/day of moderate-to-vigorous activity was assumed in both groups. To cover for a 20% dropout rate (based on earlier intervention studies conducted by our research group), we will recruit 250 patients (125 in each group) to the trial.

### Outcome measures

Objectively measured physical activity using accelerometers is the primary outcome for the intervention. Secondary outcomes include levels of HbA1c, plasma lipids, blood pressure, body composition, as well as other lifestyle factors and overall health in patients with diabetes type 2.

#### Physical activity

Physical activity and sedentary behavior is assessed using the Actigraph wGT3x-BT triaxial accelerometer (Actigraph Corporation, http://actigraphcorp.com/). To increase feasibility and maximize compliance with accelerometer measurements [19], participants are asked to wear the accelerometer on their non-dominant wrist during all hours for seven consecutive days at baseline, and at 3, 6, and 12-months follow-up. Data is sampled at a frequency of 80 Hz. Participants are also asked to keep a log over their non-wear time, e.g. when performing water activities or removing the accelerometer for other reasons. The accelerometer and log-book is mailed back to study personnel in pre-paid envelopes.

Additionally, data on daily steps will be collected from the DiaCert-app.

#### Biomarkers

HbA1c (mmol/mol), triglycerides (mmol/L), total cholesterol (mmol/L), low-density lipoprotein (LDL)-cholesterol (mmol/L) and high-density lipoprotein (HDL)-cholesterol (mmol/L) are measured in fasting blood samples at baseline and follow-up, at 3, 6, and 12 months. HbA1c is measured using the IFCC (International Federation for Clinical Chemistry and Laboratory Medicine) reference measurement procedure [20, 21]. Total cholesterol, triglycerides and HDL-cholesterol are measured using the enzymatic method. LDL-cholesterol is calculated from levels of triglycerides, total cholesterol and HDL-cholesterol using Friedewalds equation; LDL-cholesterol (mmol/L) = total cholesterol – HDL-cholesterol – (0.45*triglycerides). The ratio LDL/HDL-cholesterol is calculated from LDL- and HDL-cholesterol levels.

#### Body composition and blood pressure

Body weight (kg) and waist circumference (cm) are measured by study personnel at baseline, and follow-up at 3, 6, and 12 months. Weight is measured to the nearest 0.1 kg in light clothes with no shoes. Waist circumference is measured around the waist 2 cm above the umbilicus to the nearest cm using a non-stretchable SECA 201 tape. Height is measured at baseline to the nearest 0.5 cm. Body composition, including percentage body fat and fat free mass, is assessed at baseline and 3, 6, and 12-months follow-up at two of the participating primary health care centers. Body composition is measured using a Tanita digital body composition analyzer (Model BC-418), utilizing an 8-electrode bioelectrical impedance analysis with current going from foot-to-hand and hand-to-foot on both sides of the body.

#### Blood pressure

Blood pressure (systolic and diastolic) is measured manually by study personnel and using two electronic monitors with Bluetooth technology (Beurer BM85 and Andersson BDR 2.0). Measurements are done with participants in a seated position with legs uncrossed after the participant has been seated for at least 10 min.

#### Questionnaires

Study participants respond to paper-based questionnaires at baseline, and follow-up at 3, 6, and 12-months. The questionnaire takes approximately 60 min to complete.

*Participant characteristics* are collected using questions on civil status, education level, income, current occupation, tobacco use (smoking habits and snuff use), and diabetes related medication use. Weight and height are also self-reported prior to measurements at baseline. Smartphone use (hours/day) is assessed and participants are asked to estimate how often they bring their phone with them when they go out walking.

*Sleeping habits* are assessed using a 13-item long version of the Karolinska Sleep Questionnaire [22, 23] assessing sleeping time the previous night, stress and anxiety at time of going to bed, number of awakenings during the night and sleep quality.

*Subjectively reported physical activity* is assessed with two questions used in routine care of patients with diabetes type 2 [24]. Participants are also asked to report their time spent sitting, performing household chores and if they have been exercising during the past seven days. Participants who report to having exercised are asked about the type of activity performed and frequency and duration of performing that activity. Specifically, weight lifting, aerobics, swimming or water aerobics, and cycling are assessed. Participants can also report “other” activities performed. Additionally, participants’ intentions to change their physical activity habits are also assessed.

*Social support for being physically active* is assessed using a 5-item questionnaire adapted from the Physical Activity Social Support [25]. General support, as well as support from friends, family and colleagues is evaluated.

*Stress* is measured using the Perceived Stress Scale originally developed by Cohen et al. [26]. In the 14-item questionnaire, participants are asked to respond to how often (ranging from “never” to “very often” on a 5-point Likert scale) they perceive to react in a number of stressful situations.

*Neighborhood environment* is assessed using an adapted version of the Neighborhood Environment scale [27]. In total, 17 items including accessibility and facilitators for being physically active, such as safety, traffic and social environment in the neighborhood are included.

*Dietary intake* is measured using a validated semi-quantitative food frequency questionnaire (FFQ) [28]. Participants are asked to report, how often, on average, they consume each food and beverage, including alcohol, in the FFQ. Five additional questions used in clinical practice, developed by the Swedish National Food Agency assessing overall dietary habits are also included [29]. Drinking habits are further assessed in two questions assessing amount and intensity of consumption of alcohol [24].

*Diabetes self-efficacy and distress* is assessed using the Swedish translation of the Problem Area in Diabetes Questionnaire (Swe-PAID-20) [30]. In this 20-item questionnaire, participants rate their distress with having diabetes on a five-point Likert scale ranging from “Not a problem” to “Serious problem”.

*Health Related Quality of Life* is assessed using RAND-36 [31]. RAND-36 includes 36 questions within eight different domains and responses can be classified into a physical component summary scale and a mental component summary scale. Lastly, *purpose in Life* is assessed using a Swedish translation of The Life Engagement Test including six questions [32].

### Statistical analysis

Descriptive statistics will be used to describe characteristics of the study population at baseline. If differences in baseline characteristics are detected, potential confounders will be taken into consideration in further analysis. Data will also be checked for missing values, outliers and normality.

We will summarize pre-specified outcome measures assessed at 12 and 24 weeks of follow-up and compare intervention and control group assessing differences between groups using t-tests, ANOVAs and logistic regression. Analysis will be made following the intention-to-treat approach. Moreover, after completion of the study, follow-up assessment at week 52 will be analyzed within and between intervention and control groups to assess long-term effects. To assess the effect of both time and intervention on the outcomes, trends over time in outcomes will be analyzed using generalized estimation equations. Statistical interaction effects between characteristics and the intervention will also be tested for. Models will be adjusted for unbalanced baseline variables detected. We will also perform analysis stratified on age, sex, BMI, waist circumference, country of birth and primary health care center.

Additionally, results of usage and participants’ opinions regarding usability and satisfaction with the smartphone-app assessed using 16 questions asked at the 3-months follow-up, after the end of the active intervention, will be summarized in the intervention group and investigated in association to baseline factors, using linear and logistic regression.

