### Randomization and blinding

Study participants are randomized to either intervention group (standard care and use of the DiaCert smartphone-app) or control group (only standard care) at baseline at a 1:1 ratio by means of a random allocation sequence list generated in STATA 14.0. Women and men are randomized separately in blocks of ten within each participating primary health care center. Participants are, however, not blind to their allocation due to the nature of the intervention.

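### Covariates are to be chosen by chance baseline imbalance, which forgoes precision and leaves the adjusted model undefined; naming them in advance costs nothing

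*Protocol article*

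**What the plan says.** The Statistical analysis section of the protocol article gives the rule twice. Near its start: "If differences in baseline characteristics are detected, potential confounders will be taken into consideration in further analysis". Further on, about the models: "Models will be adjusted for unbalanced baseline variables detected". It does not say what counts as a difference or an imbalance.

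The same section says the trial will "compare intervention and control group assessing differences between groups using t-tests, ANOVAs and logistic regression", and adds that "trends over time in outcomes will be analyzed using generalized estimation equations". No covariate is named for any of these analyses.

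Under Randomization and blinding, allocation is made "at baseline at a 1:1 ratio by means of a random allocation sequence list generated in STATA 14.0", and "Women and men are randomized separately in blocks of ten within each participating primary health care center". These two stratification factors return in the analysis text only in a list of subgroup-type analyses: "We will also perform analysis stratified on age, sex, BMI, waist circumference, country of birth and primary health care center". The section on physical activity measurement shows that accelerometer activity is recorded at baseline as well as at 3, 6 and 12 months, so a baseline value of the primary outcome will exist.

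**The concern.** In a properly randomized trial, a baseline difference between arms is a chance event. It carries no information on whether the variable predicts the outcome, and predictive strength is what makes adjustment worthwhile. A rule triggered by imbalance therefore has two faults.

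- **The model varies by chance.** Which variables enter, and so which adjusted estimate is reported, depends on the particular allocation drawn. With no criterion for imbalance, two analysts could reach different models from the same data.
- **The useful covariates are mostly left out.** Baseline activity is the obvious candidate predictor of later activity, yet it enters only if the arms happen to differ on it. Sex and center are balanced by the stratified blocks, so an imbalance rule will hardly ever select them.

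The article also plans unadjusted tests and adjusted models without saying which result is the main one. At stake are the precision of the primary comparison and a clear definition of the result to be reported.

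**Working it through.** **Inputs from the article (Sample size and power considerations):** difference 8 min/day, SD 20 min/day in both groups, two-sided 5%, 80% power, "A total of 200 patients (100 in each group) completing the study", 20% dropout.

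**Assumed, not in the article:** baseline/follow-up correlation r of 0.3, 0.5 or 0.7; a trigger of p<0.05 on the baseline comparison; the number of variables screened.

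**1. The plan's own figure.** n per arm = 2 × (1.960 + 0.842)² × 20² / 8² = 98.1, so 99 against the stated 100. With 100 per arm, SE = 20 × √(2/100) = 2.83 and power = Φ(8/2.83 − 1.96) = 80.7%. Recruitment: 200 / 0.80 = 250. The sample size reproduces as an unadjusted comparison.

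**2. How often chance triggers the rule.** With k independent variables each screened at 5%, the chance of at least one flag is 1 − 0.95^k: 23% for k = 5, 40% for k = 10, 64% for k = 20.

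**3. Power with baseline activity fixed as a covariate.** The residual SD is 20 × √(1 − r²). For r = 0.5: SD = 17.32, SE = 17.32 × √(2/100) = 2.45, power = Φ(8/2.45 − 1.96) = 90.4%. The other values of r follow in the same way.

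**4. Power under the imbalance rule.** Simulation of 40,000 trials per setting, 100 per arm, adjusting for baseline activity only when its between-arm test has p<0.05.

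| r | Power, fixed ANCOVA | Power, imbalance rule | SD of estimate, fixed | SD of estimate, rule | n per arm for 80%, fixed |
|---|---|---|---|---|---|
| 0.3 | 84.3% | 80.5% | 2.7 | 2.8 | 90 |
| 0.5 | 90.4% | 81.5% | 2.5 | 2.7 | 74 |
| 0.7 | 97.7% | 82.5% | 2.0 | 2.6 | 51 |

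The fixed-ANCOVA powers come from the formula. Simulated values are 83.5%, 90.2% and 97.7%, so the gap at r = 0.3 is 3 to 4 points.

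**5. Type I error if the rule is followed mechanically.** In large samples the ANCOVA statistic is independent of the baseline statistic, and the unadjusted statistic has correlation r with it. Size = 0.05 × 0.05 + [0.05 − P(baseline and unadjusted tests both significant)].

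- r = 0.3: 0.0025 + (0.05 − 0.0049) = 4.8%
- r = 0.5: 0.0025 + (0.05 − 0.0093) = 4.3%
- r = 0.7: 0.0025 + (0.05 − 0.0165) = 3.6%

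The simulation gives 4.9%, 4.3% and 3.6%. The rule is slightly conservative.

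**6. Type I error if the choice is left open.** Worst case: the unadjusted and the baseline-adjusted results are both computed, and whichever is significant is reported. Their statistics have correlation √(1 − r²), and size = 0.05 + 0.05 − P(both significant).

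- r = 0.3: 0.10 − 0.0360 = 6.4%
- r = 0.5: 0.10 − 0.0266 = 7.3%
- r = 0.7: 0.10 − 0.0172 = 8.3%

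This bounds what the wording leaves possible. It does not predict conduct.

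**The case against.** Several points can be made for the plan, and most of them limit the concern without removing it.

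- **Error rate.** A reader might infer that data-driven adjustment inflates false positives. Applied mechanically it does the opposite (step 5). Inflation needs a selective choice between versions, which the article leaves open but does not announce; its wording on adjusting the models is directive. This stands against the stronger reading.
- **Power.** A reader might infer that the trial is underpowered. It is not: the sample size was set for an unadjusted comparison and the rule still delivers just over 80%. What is lost is a gain that was available, and its size rests on a correlation that the article does not give.
- **The longitudinal model.** If baseline is one of the time points in the generalized estimating equations, baseline activity is used whether or not it is unbalanced, and the loss may be smaller. A contrast of change from baseline has SD 20 × √(2(1 − r)): at r = 0.7 this is 15.5, with about 95% power; at r = 0.5 it is 20, with no gain over the unadjusted 80.7%. The article does not say how baseline enters, and the t-tests do not use it.
- **A filter on relevance.** The first statement of the rule is limited to potential confounders, which suggests some judgment about the outcome. The second has no such limit.
- **Baseline tests and blinding.** A reader might infer that significance tests of baseline variables are planned, or that the model is set after outcomes by arm are seen. The article promises descriptive statistics, names no baseline test, and is silent on blinding of the analysts. The rule requires only baseline data by arm.
- **An analysis plan not shown.** Such a plan might fix the covariates. But the article does not leave the matter open. It states a rule, and a plan with a fixed set would contradict it.

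**Conclusion.** The point holds as a modest, readily corrected weakness in the choice of analysis. The article commits to selecting covariates by observed imbalance, without a criterion, in a trial where imbalance is chance and the baseline value of the primary outcome is measured anyway.

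At 100 completers per arm the forgone power is about 3-4 points if r is 0.3, about 9 if r is 0.5 and about 15 if r is 0.7, under an assumed p<0.05 trigger with baseline activity as the only covariate. The planned 80% power is met throughout, and mechanical use of the rule keeps the size at about 4-5%. The second harm is that the reported result is not pinned down; the worst case for the error rate is about 6.5-8%. The documents do not support a finding of inflated type I error or of inadequate sample size.

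**What to change.** Replace both sentences with a covariate set fixed before any data by arm are seen: the baseline value of the outcome first, plus sex and primary health care center as the randomization strata. Use this set in the main between-group models, and state which model gives the primary result and how baseline enters the generalized estimating equations. Describe baseline characteristics by arm, but do not use them to select covariates. Label any model adjusted for an observed imbalance as a sensitivity analysis.

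The cost is a change of wording. The variables are already collected, no patient is affected, and the article reports that data collection is still under way, so the change can be made before analysis.

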## Methods

### Study design and recruitment

The DiaCert-study is a randomized controlled trial with two parallel arms. Patients fulfilling the inclusion criteria are recruited from five primary health care centers around Stockholm, Sweden. Each primary care center volunteered to participate in the study and data collection is performed in collaboration with clinicians and nurses at the centers. Patients that sign up for the study at the health care clinics are contacted by phone. During that contact, patients are given more information about the study. If they fulfill the inclusion criteria and agree to participate they are booked for a meeting in person at which they give their signed informed consent to participate, respond to a lifestyle questionnaire and have baseline measurements taken.

At baseline, study participants are randomized 1:1 to the intervention or control group. All participants, both in the intervention and the control group will continue to receive standard care, i.e. continue their usual care as prescribed by their primary care giver at each participating center, during the whole study period. For participants in the intervention group, the active intervention, i.e. use of the smartphone-app, last for 12 weeks from baseline. All study participants will meet with study personnel at baseline and are followed-up after the intervention at 3 and 6 months, and again after 1 year for assessment of clinical and life style factors. Physical activity is measured using the Actigraph GT3X at baseline and follow-up. For ethical reasons, participants in the control group are offered to use the smartphone-app at the 6-month follow-up if they want. Participants in the intervention group will be offered to download the app again at the same occasion if they wish to start using it again. The study design is outlined in Fig. 1.

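### Baseline values enter the group comparisons only if they look unbalanced; pre-specified adjustment for the baseline of each continuous outcome would be more precise with data already collected

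*Protocol article*

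**What the plan says.** The Statistical analysis section of the protocol article takes outcomes at 12 and 24 weeks and will "compare intervention and control group assessing differences between groups using t-tests, ANOVAs and logistic regression". No baseline value is named as a covariate. Baseline data enter by one route only: if the arms are found to differ on a baseline variable, models are adjusted for it. No criterion for imbalance is given. The same section plans GEE for the joint effect of time and intervention. It does not say whether baseline is a covariate or a time point there, and it does not rank the GEE against the t-tests and ANOVAs.

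The sample size rests on an unadjusted two-group comparison: a "difference in moderate-to-vigorous activity of 8 min/day (e.g. 22 min/day vs. 30 min/day"), with this spread: "A standard deviation of ±20 min/day of moderate-to-vigorous activity was assumed in both groups". No correlation term appears.

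Baseline values are available. The accelerometer is worn "for seven consecutive days at baseline, and at 3, 6, and 12-months follow-up". The Biomarkers section places HbA1c and lipids at baseline and all follow-ups, and the section on body composition does the same for weight and waist.

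**The concern.** In a randomized trial, observed baseline imbalance is chance. What decides whether a covariate is worth including is how well it predicts the outcome, and the baseline value of the same measurement is usually a strong predictor. A rule triggered by imbalance selects on the wrong property. It may bring in a weak predictor that happens to differ and leave out a strong one that happens not to. It also makes the final model depend on the data, with no stated threshold.

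At stake is the precision of the estimate for the primary outcome and for the continuous secondary outcomes. The sample size leaves little margin above 80% power, so a gain that needs no extra participants is worth having.

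**Working it through.** **Inputs from the article (Sample size and power considerations).** Difference 8 min/day, SD 20 min/day, two-sided 5% level, 80% power, 100 completers per arm, 20% dropout, 250 recruited. Allocation is 1:1 (Study design and recruitment).

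**Input that is assumed.** The correlation *r* between baseline and follow-up moderate-to-vigorous activity. The article gives none; 0.3 to 0.7 is shown.

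**Step 1: reproduce the plan's figures.** The standardized difference is 8/20 = 0.4. The t-based requirement is 99.08 per arm, so 100, as stated. With 100 per arm the noncentrality is 8/(20·√(2/100)) = 2.83, which gives 80.4% power. Dropout: 200/(1 − 0.20) = 250. The detectable difference by the normal approximation is 2.8016·20·√(2/100) = 7.9 min/day. The stated figures are right for an unadjusted comparison of follow-up values.

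**Step 2: adjust for baseline.** ANCOVA residual SD = 20·√(1 − r²). Power and number per arm come from the noncentral t with this SD. Detectable difference = 2.8016·SD·√(2/100).

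| Assumed r | Residual SD | Power at 100/arm | Detectable difference (min/day) | n per arm for 80% |
|---|---|---|---|---|
| unadjusted | 20.0 | 80.4% | 7.9 | 100 |
| 0.3 | 19.1 | 83.9% | 7.6 | 91 |
| 0.4 | 18.3 | 86.7% | 7.3 | 84 |
| 0.5 | 17.3 | 90.1% | 6.9 | 75 |
| 0.6 | 16.0 | 94.0% | 6.3 | 64 |
| 0.7 | 14.3 | 97.6% | 5.7 | 52 |

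The variance falls by r²: 9% at 0.3, 25% at 0.5 and 49% at 0.7. At r = 0.5, 200 completers analysed with adjustment are worth 200/(1 − 0.25) = 267 analysed without it. The table ignores the few degrees of freedom spent on covariates.

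**Step 3: would the planned GEE recover this?** Not necessarily. If baseline is an ordinary time point, a group-by-time contrast behaves much like a change score. With equal SDs at both times, the change-score SD is 20·√(2(1 − r)): 23.7 at 0.3, 20.0 at 0.5 and 15.5 at 0.7. By the same noncentral t at 100 per arm, power is 66.2%, 80.4% and 95.3%. That beats the unadjusted test only when r exceeds 0.5, and it is below ANCOVA at each of these values.

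**The case against.** **The primary-outcome baseline may not be clean.** This is the strongest objection. Participants are randomized at baseline and are not blinded. The app is demonstrated and downloaded at the baseline meeting, and the access code follows 7 days later so that app use does not overlap the baseline accelerometer week. That week therefore appears to follow allocation. If activity rises once participants know they have the app, adjusting for that week would remove part of the effect; the unadjusted follow-up comparison would not. This stands. It means adjustment is not free for the primary outcome, and the fix must carry a sensitivity analysis. It does not rescue the imbalance trigger, which would adjust for the same week precisely when the arms differ on it.

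**The trial is not underpowered.** A reader might infer that expected dropout puts the 80% at risk. The article does not support that. The power is set on this basis: "A total of 200 patients (100 in each group) completing the study". Then "we will recruit 250 patients (125 in each group) to the trial", so 20% loss is already paid for. The Trial status section lets recruitment end at a calendar date before 250 is reached, but reports no shortfall.

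**The t-test may not be the main analysis.** A reader might also infer that the unadjusted test is the declared primary analysis. The two-group form of the power calculation points that way, but the text ranks neither the t-tests and ANOVAs nor the GEE.

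**Not every outcome has a baseline.** The app usability questions are asked only at 3 months in the intervention arm, and the Blood pressure section gives no time points of its own.

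**A condensed article may leave model detail to a plan that is not shown.** That excuses silence about the GEE specification. It does not excuse the imbalance rule, which the article states as its choice.

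**Conclusion.** The point holds as a matter of efficiency. The article names tests without baseline covariates and ties adjustment to detected imbalance, although activity, HbA1c, lipids, weight and waist are measured at baseline. The unadjusted test is valid under randomization and meets its stated power, so there is neither bias nor underpowering here.

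The gain for the primary outcome depends on a correlation the article does not give. Over an assumed 0.3 to 0.7, power at 100 per arm rises from 80.4% to between about 84% and 98%; at the low end the benefit is modest. The figures also assume that the SD of 20 applies, that baseline and follow-up are linearly related, and that baseline activity is unaffected by allocation. The last assumption is doubtful for the accelerometer week. It is less of a concern for HbA1c, lipids, weight and waist, but the article gives no SDs from which to compute a gain for those.

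**What to change.** For each continuous outcome with a baseline measurement, replace the t-test or ANOVA and the imbalance trigger with one pre-specified model. This is a linear model, or a longitudinal model, of the follow-up value on arm, the baseline value of that outcome, sex and primary care centre, fitted whatever the observed balance. Sex and centre belong in it because randomization is stratified by them. Report the adjusted difference with its 95% confidence interval, and keep the t-test as supportive. State which analysis is primary and how baseline enters the GEE.

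For the primary outcome, also report the analysis without baseline activity, because the baseline wear week may follow unblinded allocation.

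Leave the sample size and the stated 80% power as they are; the 80% then serves as a conservative figure if the baseline correlation is positive.

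**Cost.** A few sentences of analysis text and no new data. The model spends a few degrees of freedom: with five centres, one for baseline, one for sex and four for centre, so six of the 198 available with 200 completers. A rule for missing baseline values is needed. The extra analysis without baseline activity has to be planned and reported.
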